In the UK, the Health in Pregnancy (HiP) grant was introduced for women reaching the 25th week of pregnancy with a due date on/or after 6 April 2009. It was subsequently withdrawn for women reaching the 25th week of pregnancy on/or after 1 January 2011. The HiP grant was a universal conditional cash transfer of £190 for women reaching 25 weeks of pregnancy if they had sought health advice from a doctor or midwife. It was designed to provide additional financial support, in the last months of pregnancy, towards a healthy lifestyle including diet, and it was suggested that the link to the requirement for pregnant women to seek health advice from a professional may provide a greater incentive for expectant mothers to seek the recommended health advice at the appropriate time. The grant was paid and administered by Her Majesty's Revenue and Customs (HMRC) on receipt of a claim form partly completed by the midwife or doctor. Advice was offered as normal by doctors and midwives. Payment was made directly into a bank account with a telephone helpline available to provide support through the claims process including options for payment in the event of difficulties opening a bank account. Take-up of the HiP grant was similar to that of child benefit (98–99%, personal communication, HMRC).

The current study focuses on the evaluation of the effectiveness and cost-effectiveness of the HiP grant. As a primary outcome, we will consider the difference in birth weight for babies born to those mothers who were eligible for the HiP grant with babies born before the HiP grant was introduced or after it was withdrawn. Specific questions the research project will address are:
Were there differential impacts of the intervention for particular subgroups defined by socioeconomic (defined in terms of both area deprivation and individual occupational social class), demographic (marital status, age, maternal height), or obstetric (parity, previous caesarean section) factors or for selected combination of these groups?Was the HiP grant cost-effective? How did cost-effectiveness vary across important subgroups identified as having differential outcomes?

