We have chosen to use data from the Scotland for this evaluation for the following reasons. First, data are available at a national level on the approximately 56 000 deliveries per year. Second, Scotland has a long history of collecting high-quality routine data. The coverage, completeness and quality of the data are considered to be very high.^46^ Third, the concentration of deprivation within parts of Scotland is unique within the UK.^47^ And using a UK-wide Carstairs index, the Scotland's population is over-represented in the bottom 5 deciles compared with England.^48^ Fourth, data on smoking at booking have been routinely recorded in Scotland for a number of years.^49^ This is not yet the case in England and Wales. The data can be linked to NRS civil registration data, which provides an estimate of completeness and contributes further information such as social class. The results will be generalisable to the rest of the UK and internationally. If the HiP grant proved beneficial in Scotland then there is every good reason to believe that a similar impact on outcomes could be achieved elsewhere and certainly in countries with similar health systems and comparable circumstances. Likewise, if the intervention was found to have been more effective for specific subgroups then we might expect subgroups to show greater benefits in other settings.

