#### Secondary outcomes

The following secondary outcomes will be assessed:
Gestation at booking;Booking before 25 weeks;Measures of size: crown to heel length, head circumference;Measures of stage: gestational age at delivery, weight-for-dates (standardised; SGA babies are those weighted less than the 5th centile weight, or LGA weighted more than the 90th centile weight), term at birth (preterm, babies are born at less than 37 weeks gestation; term babies are those born between 37 and 42 weeks gestation and post-term babies are born after 42 weeks gestation);Birth outcomes: mode of delivery, stillbirths, neonatal deaths, 5 min Apgar score. Although there is some debate concerning the robustness of the Apgar score as an outcome, it is in common use and we will therefore present results for this outcome within the context of the wide debate on the subject.

Due in part to the introduction of smoking ban in Scotland in 2006, an additional outcome of interest is maternal smoking. Maternal smoking is collected at booking and during pregnancy. The health advice given when receiving the HiP grant might have an impact on smoking rates during pregnancy over and above that of the smoke-free legislation. We will analyse the temporal change in smoking rate by socioeconomic class and its effect on outcomes.

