### Data analysis plan

#### Statistical analysis

Descriptive statistics of all variables will be presented as mean, SD, minimum, median and maximum for continuous variables and as proportions when the variables are categorical.

The main statistical design we will use is interrupted time series.^64^ Segmented regression analysis will allow an estimation of the size of the effect of the HiP grant at different time points, as well as changes in the trend of the effect over time after its implementation.

Outcomes will be measured on individual births, which are nested within mothers, with mothers themselves clustered within data zones and Health Boards. Multilevel univariable and multivariable models will be used to determine whether the outcomes changed during the period in which the HiP grants were in effect. Multilevel linear regression will be used when the outcome is continuous and multilevel binomial logistic regression when the outcome is dichotomous. Multilevel multinomial logistic regression will be used for the multicategory outcomes mode of delivery and 5 min Apgar score.

All analyses will be adjusted for temporal trends and seasonal variations in outcomes in addition to maternal age, sex of child, parity, marital status, height, weight at booking, diabetes, smoking status, gestation at booking, maternal diabetes, social class, maternal smoking and area deprivation.

The effect of HiP grant on birth weight might have a carryover effect after the withdrawal of the grant. In other words, postintervention the slope in birth weight might not fall back to the same rate as preintervention. This could be due to women who have gave birth during the intervention subsequently having a birth postintervention but still heeding the health advice given during their first pregnancy. We will carry out an additional analysis only on primiparous women to avoid such contamination.

We will analyse preterm births stratified by mode of delivery and stratified according to whether the birth was induced or spontaneous.

We will repeat the main analyses including (ie, adjusting for the effect of) ethnicity along with other covariates and compare the results with analyses excluding ethnicity to gauge the impact of this on our results. We note that the quality of this variable (including the completeness of recording) is poorer than for other variables and that only 1–2% of mothers delivering in Scotland are from minority ethnic backgrounds.

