We will conduct sensitivity analyses to increase the probability that any observed effect can be attributed to the HiP grant. The timing of the HiP grant is well-defined and fixed, therefore using the interrupted time-series approach any effects within that window can be observed. We plan to carry out three analyses for this.
We will extend this window for some months before April 2009 (births before the HiP grant was introduced).We will extend this window for some months after April 2011 (births after the HiP grant was withdrawn).We will extend the window both before and after the HiP grant period. In each case we would expect to see a dilution of any effects of the HiP grant.

The statistical analysis plan detailing the outcomes and the covariates, which will be considered for adjustment in the statistical models are presented in table 2.

**Table 2 BMJOPEN2014006547TB2:** Analysis plan detailing the outcomes and the covariates that will be considered for adjustment in the statistical models

	Primary outcome	Secondary outcomes										
	Birth weight	Booking status		Measures of stage			Measures of size:	Other birth outcomes				Maternal smoking during this pregnancy
		Gestation at booking	Booking before 25 weeks	Gestational age at delivery	Term at birth	Weight-for-dates	Head circumference,	Mode of delivery	Stillbirth	5 min Apgar score	Neonatal death	
Covariates							Crown to heel length					
*I. Measured covariates*												
A. Sociodemographic determinants												
A-1. Related to the baby												
Date of birth	Χ	Χ	Χ	Χ	Χ	Χ	Χ	Χ	Χ	Χ	Χ	Χ
Sex	Χ			Χ	Χ	Χ	Χ	Χ	Χ	Χ	Χ	
Gestational age at delivery	Χ						Χ	Χ	Χ	Χ	Χ	
Birth weight							Χ			Χ	Χ	
Mode of delivery										Χ	Χ	
A-2. Related to the mother												
Hip grant	Χ	Χ	Χ	Χ	Χ	Χ	Χ	Χ	Χ	Χ	Χ	Χ
Age	Χ	Χ	Χ	Χ	Χ	Χ	Χ	Χ	Χ	Χ	Χ	Χ
Weight at booking	Χ	Χ	Χ	Χ	Χ	Χ	Χ	Χ	Χ	Χ	Χ	
Height	Χ			Χ	Χ	Χ	Χ	Χ	Χ	Χ	Χ	
Ethnic group	Χ	Χ	Χ	Χ	Χ	Χ	Χ	Χ	Χ	Χ	Χ	Χ
Parity	Χ	Χ	Χ	Χ	Χ	Χ	Χ	Χ	Χ	Χ	Χ	Χ
Marital status	Χ	Χ	Χ	Χ	Χ	Χ	Χ	Χ	Χ	Χ	Χ	Χ
Social class	Χ	Χ	Χ	Χ	Χ	Χ	Χ	Χ	Χ	Χ	Χ	Χ
B. Medical risks of the current pregnancy and before pregnancy												
Diabetes	Χ	Χ	Χ	Χ	Χ	Χ	Χ	Χ	Χ	Χ	Χ	
Hypertension	Χ	Χ	Χ	Χ	Χ	Χ	Χ	Χ	Χ	Χ	Χ	
Infection	Χ			Χ	Χ	Χ	Χ	Χ	Χ	Χ	Χ	
Congenital anomalies	Χ			Χ	Χ	Χ	Χ	Χ	Χ	Χ	Χ	
Induction of labour									Χ	Χ	Χ	
Duration of labour									Χ	Χ	Χ	
C. Medical risks related to previous pregnancies												
Previous spontaneous abortions		Χ	Χ						Χ			
Previous stillbirths		Χ	Χ						Χ			
Previous neonatal deaths		Χ	Χ								Χ	

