D. Environmental and behavioural risks												
Income domain of the SIMD	Χ	Χ	Χ	Χ	Χ	Χ	Χ	Χ	Χ	Χ	Χ	Χ
Urban/rural status of the area of residence	Χ	Χ	Χ	Χ	Χ	Χ	Χ	Χ	Χ	Χ	Χ	Χ
Booking status (gestational age at booking, booking before 25 weeks)	Χ			Χ	Χ	Χ	Χ	Χ	Χ	Χ	Χ	Χ
Smoking status (before and during this pregnancy)	Χ	Χ	Χ	Χ	Χ	Χ	Χ	Χ	Χ	Χ	Χ	
Typical weekly alcohol consumption (before and during this pregnancy)	Χ	Χ	Χ	Χ	Χ	Χ	Χ	Χ	Χ	Χ	Χ	Χ
Drug misuse during this pregnancy	Χ	Χ	Χ	Χ	Χ	Χ	Χ	Χ	Χ	Χ	Χ	Χ
*II. Unmeasured covariates*												
Maternal weight gain												
Maternal nutrition												
Maternal education												
Maternal exposure to stress												
Maternal physical activity												
Exposure to toxic substances												
Birth interval												
History of preterm birth												
Statistical methods												
Multilevel linear regression	Χ	Χ		Χ			Χ					
Multilevel binomial logistic regression			Χ			Χ			Χ		Χ	Χ
Multilevel multinomial logistic regression					Χ			Χ		Χ		

Χ: variables which will be considered for adjustment in the statistical analysis.

SIMD, Scottish Index of Multiple Deprivation.

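### The birth-weight model adjusts for smoking during pregnancy and gestation at booking, which the grant may itself change, and no model is clearly planned for the total effect

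*Protocol article*

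**What the plan says.** The primary question (Introduction) compares the birth weight of babies whose mothers were eligible for the grant with that of babies born before its introduction or after its withdrawal.

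The Statistical analysis section says all analyses will be adjusted for trend, season and a covariate list that includes "smoking status, gestation at booking, maternal diabetes, social class, maternal smoking and area deprivation". Table 2 marks two relevant rows for birth weight: "Smoking status (before and during this pregnancy" and "Booking status (gestational age at booking, booking before 25 weeks". The sentence introducing Table 2 is softer and calls these "covariates, which will be considered for adjustment in the statistical models".

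The article also presents both variables as possible effects of the grant:
- **Booking.** The Introduction says the link to health advice may "provide a greater incentive for expectant mothers to seek the recommended health advice at the appropriate time". Gestation at booking and booking before 25 weeks are secondary outcomes.
- **Smoking.** Under Secondary outcomes: "The health advice given when receiving the HiP grant might have an impact on smoking rates during pregnancy". Maternal smoking during this pregnancy has its own outcome column in Table 2.

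A separate smoking analysis is planned: "We will analyse the temporal change in smoking rate by socioeconomic class and its effect on outcomes".

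**The concern.** A variable that the intervention can change, and that in turn affects birth weight, lies on the causal path. Conditioning on it removes from the grant coefficient whatever part of the effect runs through it. The remaining coefficient answers a narrower question than the one in the Introduction, and nothing in the article says that the narrower question is wanted.

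Three uses of the result depend on this:
- the primary conclusion on birth weight;
- the two-sided test meant to detect harm, whose sidedness is right but which would be applied to a partial effect;
- the birth-weight input to the cost-effectiveness model in the Economic analysis section.

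**Working it through.** **1. The plan's own figure.** Sample size states power 0.90 for 7 g, with 56,000 births a year, 6505 data zones and an intraclass correlation of 0.05. No birth-weight SD is given, so the figure cannot be reproduced uniquely. I assumed an SD of 450 to 600 g.
- Births in the 25 grant months: 25 × 56,000/12 = 116,667. Births in the other 95 months: 443,333.
- SE = SD × √(1/116,667 + 1/443,333) = SD × 0.00329, times the square root of the design effect.

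| Cluster size used in the design effect | Design effect | Power for 7 g |
|---|---|---|
| No clustering | 1.00 | 0.94–0.997 |
| Births per zone per year | 1.38 | 0.86–0.98 |
| Births per zone in grant period | 1.85 | 0.74–0.94 |
| Births per zone, all 10 years | 5.25 | 0.34–0.54 |

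The point does not depend on which row was used. Step 4 takes the stated 0.90 as given.

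**2. Scale of the smoking path.** The Introduction gives a reduction of 162 to 377 g for smoking during pregnancy. One percentage point of prevalence therefore moves the mean by 1.6 to 3.8 g. A shift of 7 g needs 7/377 = 1.9 to 7/162 = 4.3 points. This applies the full deficit to each woman whose smoking changes. Women who stop late may gain less, and then more points are needed.

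**3. What adjustment does to the coefficient.** I used simulated births with a linear trend, assuming 20% smoking, residual SD 520 g and a 2 g effect not acting through smoking.

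| Fall in smoking | Deficit | True total | Trend only | Trend + smoking |
|---|---|---|---|---|
| 2 points | 162 g | 5.2 g | 5.1 g | 1.8 g |
| 4 points | 270 g | 12.8 g | 13.6 g | 2.7 g |

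Within simulation error, adding smoking returns the 2 g remainder, not the total.

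**4. Illustrative power.** Power 0.90 implies effect/SE = 1.960 + 1.282 = 3.242 at 7 g. If a share s of a 7 g effect acts through fully recorded smoking, a fraction f = 1 − s is left, and power = Φ(3.242f − 1.960) + Φ(−3.242f − 1.960).
- s = 25%: 5.25 g left, power 0.68
- s = 50%: 3.50 g left, power 0.37
- s = 75%: 1.75 g left, power 0.13

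If only 75% of smokers are recorded and prevalence is 20% (both assumed), (1 − 0.75)/(1 − 0.75 × 0.20) = 29% of the smoking path survives adjustment. The three powers become 0.76, 0.56 and 0.33. The shares are assumptions; the document gives none.

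**5. When the paths oppose.** Suppose the smoking path adds 7 g and another path takes off 3 g. The total is 7 − 3 = +4 g, but the smoking-adjusted coefficient is −3 g. If the other path takes off 7 g, the total is 0 and the adjusted coefficient is −7 g.

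**6. Which smoking measure matters.** With a true +7 g effect arising only from quitting after booking (assumed 20% smoking at booking, SD 550 g), adjusting for smoking at booking left the estimate at 6.8 to 7.2 g. Adjusting for smoking during pregnancy left −0.2 to 0.2 g. Monte Carlo SE was 0.3 to 0.7 g.

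**7. Booking.** The document gives no effect of booking time on birth weight, so this path cannot be sized.

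**The case against.** **The adjustment set may be less fixed than it looks.** Read literally, the text would adjust smoking for smoking. Table 2 leaves that cell blank, so the sentence is shorthand, and Table 2 only lists covariates for consideration. The text does not say which smoking measure it means. Study population notes that "data on smoking at booking have been routinely recorded in Scotland for a number of years", and step 6 shows that measure removes nothing from a change after booking. The section also mentions univariable models and a simplest model adjusting for factors such as marital status. This stands in part. But Table 2 expressly includes smoking during this pregnancy, the text expressly includes gestation at booking, and no model is clearly stated to carry trend and season without them.

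**Adjustment has a rationale.** There is no concurrent control. The article reports changes in booking policy discussed from 2008 and required by March 2011, close to the grant window. Without gestation at booking, part of that change may be credited to the grant. Smoking is also a reasonable control for the 2006 ban. This stands, and it is why the reduced model should sit beside the current one and not replace it.

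**Mediator changes would be visible anyway.** Smoking and booking are analysed as outcomes, and the economic model admits affected secondary outcomes. That is true, but it does not restore the missing part to the birth-weight coefficient or to the harm test.

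**The size is hypothetical.** At an assumed 20% prevalence, 1.9 to 4.3 points is a relative change of about 9 to 22%. The Introduction says advice was given as normal, and Sample size says 7 g is not a threshold of clinical importance. This stands; steps 2 to 4 give scale only.

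**Conclusion.** The point holds as one about what is estimated. If the grant changed smoking during pregnancy or booking, the adjusted birth-weight coefficient is not the total effect the Introduction asks about. A smoking change of 1.9 to 4.3 points corresponds to 7 g. Whether such a change occurred, and how much of any effect ran through it, is unknown from the document.

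Three stronger readings are tempting, and the document does not support them:
- **That adjustment always understates benefit or harm.** This is so only when the paths share a sign (step 5).
- **That the study's power is really 0.37 or 0.13.** Those values rest on assumed shares and on an SE taken from a figure that cannot be reproduced.
- **That the reduced model is free of bias and should stand alone.** It is exposed to the booking policy change. Weight at booking is not free of the problem either, since its recorded value depends on when booking occurs.

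The path through nutrition, the grant's stated route to birth weight, is not removed by these two adjustments.

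**What to change.** In the Statistical analysis section:
1. Add a birth-weight model with the grant term, trend, season and the covariates in the text's list, but without smoking during pregnancy and gestation at booking. Label it the total-effect estimate.
2. Report the current model beside it, labelled as the effect not acting through those variables.
3. State which smoking measure each model uses. Smoking before pregnancy, where recorded, or at booking may stay as a control for the 2006 ban.
4. Show the total-effect model with and without weight at booking.
5. Base the harm statement and the birth-weight input to the Economic analysis on the total-effect estimate, with the other model as sensitivity.

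The cost is a wording change and a few extra fits on variables already planned. Smoking before pregnancy appears only in Table 2, so its availability needs checking. The downside is that the total-effect estimate may absorb part of the 2008–2011 booking policy change. Neither the trend term nor the April 2006 restriction fully deals with that, so both estimates must be shown.

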### Study population

The population under study will be all singleton births in Scotland over the periods of January 2004 to March 2009 (preintervention), April 2009 to April 2011 (intervention) and May 2011 to December 2013 (postintervention).

The Scottish maternity and neonatal database is a comprehensive record linkage system.^40^
^41^ Probabilistic linkage procedures are used to add a unique identifier to all data sets to ensure all relevant records relating to an individual can be linked as required. It facilitates the linkage of a number of records from the system of Scottish Morbidity Records (SMR) including mother's obstetric records (SMR02) and the baby's birth and neonatal information from Scottish Birth Records (SBR).^42^ Further links to the stillbirth and infant Death Survey and the National Records of Scotland (NRS) birth, stillbirth and infant death records can be carried out. The coverage is almost all births in Scotland.^43^ From NRS data, we know of all registered births in Scotland (ie, 100%). We have suitable record linked data on 98% of these births.^44^ These will nearly all be hospital births; a fairly high proportion of the missing records are home births.

There is an average of about 56 000 births per year in Scotland.^45^ The analysis period 2004–2013 should yield over 585 000 births. The analysis period 2006–2013 should yield over 455 000 births.

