The simplest model for the intervention effect will include a dummy variable ‘intervention’ covering the period from the introduction to the withdrawal of HiP grants, with adjustment for relevant factors such as marital status. (More complex models of the effect of the intervention will include an interaction of the intervention with the temporal trend.) Before carrying out specific subgroup analysis, we will identify differential effects by fitting interaction terms. An assessment as to whether there is a differential effect of the intervention for single women, for example, will involve a test of the significance of the intervention between marital status and the intervention effect. If the interaction is significant this will aid our understanding of the generalisability to other populations, including the rest of the UK. Subgroup analyses will be conducted for those groups seen as having the greatest potential to benefit from the payments such as those living in the most deprived areas, those in the lowest social classes, lone mothers, primiparous women, teen mothers, mothers from ethnic minorities and selected combinations of these groups. For each group we will replicate the main analysis. This reduction in sample size for subgroup analyses will result in fewer women/births being available but the same number of areas (data zones) will be analysed (apart from analyses restricted to those living in the most deprived areas).

An increase in birth weight, although desirable at a population level, may not be a beneficial outcome if the baby were already at risk of being LGA. Separate subgroup analyses will therefore be conducted for women seen to be at high risk of delivering a LGA baby (women with diabetes) and for the remainder of the population. Given that some subgroups may contain small numbers, and bearing in mind the potential importance of the intervention, we will report the results of all subgroup analyses and not just those that reach statistical significance to avoid false negatives. The above process will involve conducting many tests, which will not be independent of each other. Rather than adjusting CIs or p values to account for this we will present the results of all analyses and caution the user regarding the interpretation of the results. Indeed, some statisticians recommend never correcting for multiple comparisons while analysing data.^65^

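### The primiparous-only analysis gives a first-birth estimate free of the described carry-over, but cannot show whether carry-over dilutes the all-women estimate

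*Protocol article*

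**What the plan says.** All references are to the protocol article.

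- **The mechanism.** The Statistical analysis section says the postintervention slope may not return to its earlier rate. It offers as a possible cause "women who have gave birth during the intervention subsequently having a birth postintervention but still heeding the health advice given during their first pregnancy".
- **The remedy.** One extra analysis: "We will carry out an additional analysis only on primiparous women to avoid such contamination".
- **The subgroup list.** The same section plans subgroup analyses for "those groups seen as having the greatest potential to benefit from the payments", with examples that include "those in the lowest social classes, lone mothers, primiparous women, teen mothers", and says the main analysis will be repeated in each group. The Introduction separately asks whether the effect differs by parity.
- **The models.** The simplest is a dummy for the grant period. More complex versions interact it with the time trend. Segmented regression over the three periods is also named.
- **The data structure.** "Outcomes will be measured on individual births, which are nested within mothers". The Study population section describes record linkage. Table 2 lists birth interval as an unmeasured covariate.

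The article does not say how a difference between the primiparous and all-women results would be interpreted.

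**The concern.** The contamination described is narrow. It can sit only in postintervention births to mothers who also gave birth while the grant existed. The restriction removes every parous birth in all three periods.

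The fit that remains is also the primiparous subgroup fit planned elsewhere in the section. One estimate therefore serves two purposes: benefit in a group thought likely to respond, and freedom from carry-over. If it exceeds the all-women estimate, carry-over may have diluted the latter, or first-time mothers may have gained more. What is at stake is the reading of the all-women estimate, which is the one that matters for a universal grant. A true parity difference could be taken for dilution, or the reverse.

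**Working it through.** The plan gives no figure for the carry-over check, so there is none to reproduce. Its 7 g is taken as given, because the SD behind it is not stated.

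**1. How much of what is left out could be contaminated?**
The Study population section gives 63 months before the grant, 25 during and 32 after: 63 + 25 + 32 = 120. Contamination needs a postintervention birth. With stable monthly numbers of parous births, the share that cannot be contaminated is at least (63 + 25)/120 = 88/120 = 73.3%.

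**2. How large could the dilution be?**
Assumptions not in the article: 45% first births; 30-45% of postintervention parous births contaminated; the full effect carried over; no underlying trend, so comparator months are weighted equally.
- Contaminated share of all births: 32/120 × 0.55 × (0.30 to 0.45) = 4.4-6.6%. The restriction leaves out 55%.
- Contaminated share of comparison births, which equals the proportional dilution of the on/off effect: 32/95 × 0.55 × (0.30 to 0.45) = 5.6-8.3%.
- A simulation with assumed lognormal birth intervals (median 24-42 months, log-SD 0.4-0.6) put contamination higher, at 37-61%. The dilution is then 32/95 × 0.55 × (0.37 to 0.61) = 6.9-11.3%.

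**3. Can the check separate the two explanations?**
Take an illustrative 20 g effect in primiparous women.
- *Scenario A, carry-over only:* 20 g in parous women too, with half of postintervention parous births keeping the full effect. The parous on/off effect is 20 × (1 − 0.5 × 32/95) = 16.6 g.
- *Scenario B, parity difference only:* no carry-over, and a true parous effect of 16.6 g.

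In either case the all-women on/off estimate is 0.45 × 20 + 0.55 × 16.63 = 18.15 g.

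| Contrast of period means | A: carry-over | B: parity difference |
|---|---|---|
| On/off, primiparous | 20 g | 20 g |
| On/off, parous | 16.6 g | 16.6 g |
| On/off, all women | 18.15 g | 18.15 g |
| Introduction step, parous | 20 g | 16.6 g |
| Withdrawal step, parous | 20 − 0.5 × 20 = 10 g | 16.6 g |

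The on/off rows are identical, so neither the primiparous-versus-all gap (1.85 g) nor the parity interaction distinguishes A from B. The introduction and withdrawal rows do.

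The withdrawal contrast alone does not settle it. Under A it is 0.45 × 20 + 0.55 × 10 = 14.5 g in all women, and a true parous effect of 10 g with no carry-over gives the same 14.5 g. The introduction step is needed as well.

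**4. What does the restriction cost in precision?**
The Sample size section uses 56 000 births a year, 6505 data zones and an intraclass correlation of 0.05. Keeping 45% of births in the same zones shrinks the clusters, so with design effect DE = 1 + (m − 1) × 0.05 the detectable effect becomes 7 × √[DE(0.45m)/(0.45 × DE(m))].
- Annual clusters: m = 8.6 falls to 3.9 and DE 1.38 to 1.14, giving 7 × √[1.14/(0.45 × 1.38)] ≈ 9.5 g.
- Ten-year clusters: m = 86 falls to 39 and DE 5.25 to 2.89, giving 7 × √[2.89/(0.45 × 5.25)] ≈ 7.7 g.

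**The case against.** The strongest defence is that the plan says avoid, not test. First-time mothers have no earlier birth, so the restriction does what is claimed for it. Dropping parous births in every period also keeps the periods comparable on parity, and because the analysis is additional the primary analysis loses no data. All of this stands. A reader might infer that the primiparous analysis is invalid or should be replaced; the article does not support that.

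A second defence is that the design holds the information needed. A parity difference appears when the grant is introduced, whereas this carry-over can appear only after withdrawal. Segmented regression and parity interactions are both planned. This also stands, so it would be too strong to say that the study cannot separate the two explanations. The limit lies in the on/off dummy and in comparing the primiparous and all-women results. The article does not describe using the introduction step by parity for this purpose, and its analyses with a widened grant window probe timing rather than previous exposure.

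Third, primiparous women are one of several examples on the subgroup list, so the plan does not predict that they benefit most. Overlap with that list is enough for the ambiguity.

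Finally, an exposure flag has its own weaknesses. Linkage is probabilistic, covers 98% of births and is confined to Scotland, while the grant was UK-wide. Excluding flagged births would remove short-interval mothers from one period only. These are reasons to add the flag alongside the primiparous analysis rather than in its place.

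**Conclusion.** The point holds in a limited form. The primiparous analysis is a valid first-birth estimate free of the described carry-over. It is not evidence on whether the all-women estimate is diluted, because under the on/off dummy carry-over and a parity difference give the same results.

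The firmest figure is that at least 73% of the parous births left out precede withdrawal; it rests only on stable monthly births. The 6-8% dilution rests on the assumed 45% first births, 30-45% contamination, full carry-over and no trend, and reaches about 11% at the top of the simulated range. The effect on the main estimate is therefore likely to be modest.

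Two larger figures might be inferred and should not be used. Scaling 7 g by 1/√0.45 gives 10.4 g, but this ignores the smaller design effect; 7.7-9.5 g is the better range. Supposing effects of 15 g and 5 g by parity makes the main estimate look 37% diluted, but that only restates the supposed split. This is a cheap improvement to a secondary analysis, not a flaw in the primary one.

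**What to change.** In the Statistical analysis section:

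1. Keep the primiparous analysis, described as an estimate for first births free of this carry-over. State that a primiparous-versus-all difference alone will not be read as evidence of carry-over.
2. Add an analysis in all births. Use the mother identifier to flag postintervention births to mothers with an earlier birth in April 2009 to April 2011, and fit the flag as a separate term in the main model.
3. Include interval since the previous birth, derived from linked dates of birth, so that the flag does not merely pick up short intervals. Amend the Table 2 entry that lists it as unmeasured.
4. If flagged births are also excluded, apply a matching birth-interval exclusion in the earlier periods.
5. Report the introduction and withdrawal steps separately by parity, since only the withdrawal step can carry this contamination.

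The cost is one exposure flag, an interval derived from data already linked, and a few extra model fits. The flag window lies inside the study period, but intervals for births early in the series will have incomplete look-back and need earlier records or a missing category. Earlier births that are unlinked or took place outside Scotland will be missed.
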